### Sample size and power calculations

At present there is insufficient preliminary data demonstrating an accurate effect size of AT1 blockers on AAA growth. In line with other AAA drug trials, we estimated our sample size based on a clinically relevant reduction of 30 % in annual AAA growth [18]. Given local AAA growth rates (mean = 1.20 mm/y, standard deviation = 1.16) applicable to the study population, we calculated an effect size d = 0.36 [54]. Accordingly, based on t-test analysis, this study requires 126 participants per group (252 in total, power = 80 %, α = 0.05) to detect the hypothesised reductions in AAA growth. Taking into account a 24-month drop-out rate of approximately 20 %, we plan to recruit 300 patients.

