The DSMB will consist of an independent epidemiologist, vascular surgeon and statistician; and will meet to assess all adverse events. In particular, the DSMB will concentrate on AAA-related events such as sudden death due to AAA rupture, as well as adverse events related to study medication. Expected AAA rupture rates for small AAAs are approximately 1 to 2 % per year based on published data [9, 10]. Rupture rates greater than this will be considered to be a cause for concern. In this instance consideration will be given to assessment of all other outcome data from the study. AAA growth will be compared between placebo and telmisartan groups using this data. The final decision to stop the study will take into account AAA ruptures, AAA growth data and any other serious complications. Following their assessment, the DSMB would report their recommendation to the steering committee. One formal interim analysis will be undertaken when 60 % of participants have been followed-up for 24 months. Based on all available data at the time of the interim analysis, the difference in growth at 24 months of follow-up will be estimated and tested.

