It is possible that participants randomised to telmisartan may have a small reduction in blood pressure. In the event that the control group are more frequently receiving other blood pressure modifying medications at the completion of the trial, post-hoc analyses will be conducted with appropriate adjustment for these confounding factors.

The stopping boundaries are based on the alpha and beta spending function theory and the stopping rule preserves the overall probability of 0.05 of rejecting the null hypothesis in favour of telmisartan while the null hypothesis is true [57]. The stopping rule is flexible in the sense that the actual time of the interim analyses may deviate from the scheduled time and that more interim analyses may be inserted. The stopping rule is designed using SAS PROC SEQDESIGN. We have chosen a gamma cumulative spending function with gamma parameter equal to −5 for alpha and −7 for beta. These choices lead to conservative stopping boundaries, such that the trial will stop for superiority only if the evidence for a favourable telmisartan effect is very strong and the trial will stop for futility only if the interim analysis suggests it very unlikely that a significant telmisartan effect will be found at the end of the trial. At the interim analysis, the trial will stop for superiority if the one-sided *P* value in favour of telmisartan is smaller than 0.0032. The trial will stop for futility if the one-sided *P* value is larger than 0.5.

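### The stopping rule claims an overall error of 0.05 in favour of telmisartan, but its own interim boundary of 0.0032 follows from 0.025 in that direction

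*Protocol article*

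**What the plan says.** All the elements are in the protocol article.

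- **Overall error** (Statistical analysis): "the stopping rule preserves the overall probability of 0.05 of rejecting the null hypothesis in favour of telmisartan while the null hypothesis is true". As worded, this is an error probability in one direction.
- **Spending functions** (Statistical analysis): a "gamma cumulative spending function with gamma parameter equal to −5 for alpha and −7 for beta".
- **Superiority boundary** (Statistical analysis): the trial stops if the one-sided P "value in favour of telmisartan is smaller than 0.0032". The futility boundary is a one-sided P above 0.5, given to one decimal.
- **Interim timing** (Safety): "One formal interim analysis will be undertaken when 60 % of participants have been followed-up for 24 months".
- **Sample size** (Sample size and power calculations): "this study requires 126 participants per group (252 in total, power = 80 %, α = 0.05". The section does not say whether this alpha is one-sided or two-sided.

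The article gives no final critical value. It also allows the interim time to shift and further looks to be added.

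**The concern.** An alpha-spending function turns an overall error and an information fraction into an interim boundary. Here the overall error, the function, the planned timing and the boundary are all stated, so they can be checked against each other. They do not agree: the boundary is half of what the stated error level would produce.

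What is at stake is mainly the final test. The final critical value depends on the overall error, and so would any boundary recalculated because the interim moved or a look was added. An analyst who takes 0.05 in favour of telmisartan from the sentence and one who works back from 0.0032 would arrive at different success thresholds. A final one-sided P between about 0.024 and about 0.049 would be a success under the sentence and a failure under the design behind the boundary.

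**Working it through.** **Inputs.** Alpha gamma −5, beta gamma −7, superiority boundary 0.0032 and futility boundary 0.5 (Statistical analysis); interim at 60 % of participants (Safety), taken as information fraction t = 0.60; 80 % power (Sample size and power calculations).

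**Step 1: reproduce the stated boundary.** The share of alpha spent at t under gamma −5 is

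f(t) = (e^(5t) − 1) / (e^5 − 1).

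At t = 0.60: (e^3 − 1) / (e^5 − 1) = 19.086 / 147.413 = 0.1295.

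| Overall error in favour of telmisartan | Interim one-sided P | Against the stated 0.0032 |
|---|---|---|
| 0.025 | 0.1295 × 0.025 = 0.00324 | matches after rounding |
| 0.05 | 0.1295 × 0.05 = 0.00647 | twice the stated value |

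**Step 2: could timing explain the gap?** Solving for the t that gives exactly 0.0032 yields t = 0.598 with 0.025, and t = 0.469 with 0.05. The first is the planned timing; the second is well short of it. At t = 0.55 an overall 0.05 would still give 0.0050, and at t = 0.65 it would give 0.0084.

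**Step 3: does the futility boundary discriminate?** The share of beta spent is (e^4.2 − 1) / (e^7 − 1) = 65.686 / 1095.633 = 0.0600. The futility Z is θ√0.6 + z(0.0600 × β), where θ is the drift that gives the two-look design its power. Solving with the bivariate normal distribution (correlation √0.6):

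| Overall error in favour of telmisartan | Futility P, 80 % power | Futility P, 90 % power |
|---|---|---|
| 0.025 | 0.532 | 0.497 |
| 0.05 | 0.628 | 0.594 |

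Both values in the 0.025 row round to the stated 0.5. Neither value in the 0.05 row does. Binding or non-binding futility changes these by less than 0.001.

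**Step 4: what follows for the final test.** With non-binding futility, the final critical value u2 solves

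α1 + P(Z1 < u1, Z2 > u2) = α,

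where α1 is the alpha spent at the interim and u1 the matching Z.

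- α = 0.025: α1 = 0.00324, u1 = 2.723, u2 = 1.976, one-sided P about 0.024.
- α = 0.05: α1 = 0.00647, u1 = 2.485, u2 = 1.659, one-sided P about 0.049.

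Binding futility gives 1.975 and 1.658. The figures for 0.05 follow the stated spending function throughout. Keeping 0.0032 at the interim and spending the rest of 0.05 at the end would give Z of about 1.65, but that departs from the stated function.

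**The case against.** The best defence is that this is loose wording of an ordinary two-sided 0.05 design. The number that governs the interim is 0.0032. It is correct for 0.025 in one direction and stricter than the sentence would allow, so the interim decision is not made more lenient. The article nowhere states a one-sided final test at 0.05, and a condensed article may leave the final critical value to the analysis plan. All of this stands. It means that no stated boundary is shown to be wrong, and that a doubled false-positive rate is the consequence of one literal reading and not something the design has fixed. It does not rescue the sentence, which states an error level that the boundary in the same paragraph contradicts.

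Treating 60 % of participants as 60 % information is an assumption. It does not help the sentence: the interim uses all available data, so participants with partial follow-up would, if anything, raise the information fraction, whereas an overall 0.05 needs it to fall to about 47 %.

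A reader might infer two stronger points that the article does not support.

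- **That the futility boundary of 0.5 shows a design at 90 % power, contradicting the stated 80 %.** At t = 0.60, 90 % power does fit more closely (0.497 against 0.532). But the boundary is printed to one decimal, both values round to it, and at t = 0.62 a design with 80 % power gives 0.495. The figure cannot tell the two apart.
- **That the sample size proves a two-sided test.** With the stated effect ("we calculated an effect size d = 0.36"), a t-test at 80 % power needs 123 per group at two-sided 0.05 and 97 at one-sided 0.05, so 126 looks two-sided. But the section's own inputs ("Given local AAA growth rates (mean = 1.20 mm/y, standard deviation = 1.16) applicable to the study population") with a 30 % reduction give 0.30 × 1.20 / 1.16 = 0.31. At that effect, one-sided 0.05 needs 130 per group and two-sided 0.05 needs 164. The sample size does not settle sidedness, and the finding does not rest on it.

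**Conclusion.** The sentence on overall error is wrong as written. The stated superiority boundary follows from 0.025 in favour of telmisartan, and the futility boundary also fits 0.025 but not 0.05. The most likely explanation is that a two-sided 0.05 was described as a one-directional error.

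The size is a factor of two in the false-positive rate in favour of telmisartan (5 % instead of 2.5 %), with final one-sided thresholds of about 0.049 and about 0.024. That cost arises only if the final critical value, or a recalculated boundary, is taken from the sentence. The conclusion assumes one interim at 60 % information and the gamma functions as stated. The final thresholds would shift a little if the interim moved or looks were added.

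**What to change.** Change the sentence to give an overall probability of 0.025 in favour of telmisartan (0.05 two-sided), and derive the final critical value from that: one-sided P of about 0.024 if the interim falls at 60 % information. The interim boundaries can then stay as printed, and the cost is one sentence.

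If 0.05 in one direction is really intended, keep the sentence and recompute both interim boundaries. On the stated functions at 60 % information and 80 % power, superiority would move to about 0.0065 and futility to about 0.63. That costs one run of the sequential design procedure and a change to the printed figures.

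Either way, the choice should be made before any unblinded comparison. The article reports that recruitment is still under way, so this can be settled without a choice between two success thresholds once results are known.

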## Discussion

A number of randomised control trials have been undertaken to examine the efficacy of AAA growth-limiting drugs. To date, no medication has demonstrated efficacy in reducing AAA growth convincingly. TEDY is the first clinical trial to address whether AT1 blockers can limit AAA progression in humans. Another trial is assessing the influence of an ACE inhibitor on AAA progression [58]; however, the mode of action of AT1 blockers and ACE inhibitors are not analogous. A large population study reported that ACE inhibitor prescription was associated with less likelihood of presenting with a ruptured AAA [59]. Another study, however, found ACE inhibitor prescription to be associated with increased AAA expansion [60]. There is preliminary evidence from animal studies, observational studies in humans, and randomised trials on Marfan’s disease to suggest that AT1 blockade will limit AAA growth in humans [32, 45–48]. If successful, TEDY will confirm the central role of the angiotensin pathway in AAA pathogenesis, and provide the first growth limiting drug for secondary prevention of AAA.

## Trial status

Participants are currently being recruited.

## Abbreviations

AAA: abdominal aortic aneurysm
ACE: angiotensin-converting enzyme
AT1: angiotensin II receptor type 1
CRF: case report form
CTA: computed tomographic angiography
DSMB: Data and Safety Monitoring Board
MMP-9: matrix metalloproteinase-9
OPG: osteoprotegerin
OPN: osteopontin
SAE: serious adverse event
SF-36: Short Form-36
TEDY: Telmisartan in the management of abdominal aortic aneurysm
TGF-β1: transforming growth factor-beta1
